# The effectiveness of intratympanic injections with methylPREDnisolon versus placebo in the treatment of vertigo attacks in MENière’s disease (PREDMEN trial): a study protocol for a phase-3 multicentre, double-blinded, randomised, placebo-controlled trial

**DOI:** 10.1136/bmjopen-2023-076872

**Published:** 2024-08-29

**Keywords:** otolaryngology, adult otolaryngology, randomized controlled trial

## Abstract

**Introduction:**

Intratympanic corticosteroids are commonly used in the treatment of Menière’s disease (MD). However, few and small randomised controlled trials (RCT) on the effectiveness of intratympanic corticosteroids have been performed. A recent Cochrane review suggested that a well-conducted placebo-controlled RCT with a large study population is required to evaluate the effectiveness of the use of intratympanic corticosteroids in MD. The following protocol describes a phase-3 multicentre, double-blinded, randomised, placebo-controlled trial to compare the effectiveness of methylprednisolone (62.5 mg/mL) to a placebo (sodium chloride 0.9%).

**Methods and analysis:**

We aim to recruit 148 patients with unilateral MD from six hospitals in the Netherlands. Patients will be randomly assigned to either the methylprednisolone or the placebo group. Two injections will be given, one at baseline and one after 2 weeks. Follow-up assessments will be done at 3, 6, 9 and 12 months. The primary outcome will be the frequency of vertigo attacks. Attacks will be evaluated daily with the DizzyQuest app. Secondary outcomes include hearing loss, tinnitus, health-related quality of life, use of co-interventions and escape medication, (serious) adverse events and cost-effectiveness. These will be evaluated with audiometry and multiple commonly used, validated questionnaires. For the primary and secondary outcomes mixed model analysis, generalised estimating equation analysis and logistic regression analysis will be used.

**Ethics and dissemination:**

This study was submitted via the Clinical Trials Information System, reviewed and approved by the Medical Research Ethics Committee Leiden The Hague Delft and the local institutional review board of each participating centre. All data will be presented ensuring the integrity and anonymity of patients. Results will be published in scientific journals and presented on (inter)national conferences.

**Trial registration number:**

This study is registered at ClinicalTrials.gov Protocol Registration and Results System, with the registration ID: NCT05851508.

STRENGTHS AND LIMITATIONS OF THIS STUDYIn this randomised placebo-controlled study, both participants and clinicians will remain blinded throughout the follow-up period, therefore, minimising the risk of bias.The prospective design with patients daily recording their vertigo attack directly in an app lowers the risk of missing data and recall bias.This study includes a rather large patient population of 148 patients.Vestibular migraine and Menière’s disease (MD) share multiple features in terms of clinical presentation and other symptomatology, distinguishing between the two could be challenging and therefore, could form a possible limitation in this study.Subanalyses on clinical subgroups of MD (autoimmune, familial and MD+migraine) will be difficult to conduct because many patients cannot be classified in a subgroup or are part of multiple subgroups.

## Introduction

 Menière’s disease (MD) is a clinical condition characterised by tinnitus and aural fullness, low-frequency to mid-frequency sensorineural hearing loss, and spontaneous episodes of vertigo that can last 20 min to 12 hours.^1^ Patients with MD experience a worse quality of life than healthy patients due to vertigo, tinnitus and hearing loss.^2^ In addition, higher levels of anxiety and depression are seen in patients with MD.^3^

Although its aetiology is unknown, endolymphatic hydrops (EH) is thought to be associated with MD. Almost all patients with MD have EH, but not all patients with EH have symptoms of MD. It is unknown if EH is a result of MD or a causal factor for MD.^4 5^ Until this day, there is no agreement as to the ideal treatment of MD due to the lack of evidence for the effect of various therapies. Current treatment consists of dietary and lifestyle modifications, oral diuretics, vestibular rehabilitation for chronic imbalance, intratympanic therapy and/or ablative surgery.^1^ With intratympanic gentamicin and corticosteroid injections, the drug is directly delivered into the middle ear, from where it will be absorbed in the inner ear. Unlike gentamicin, corticosteroid therapy does not carry a risk of causing hearing loss. Therefore, it is currently the first step of standard care in the treatment of MD.^1^ Although the mechanism of action of steroids on the inner ear remains speculative, it may improve cochlear blood flow and stabilise the vascular endothelium which enhances fluid homeostasis by upregulation of cochlear ion gene expression.^6^ Recently, a Cochrane review was published evaluating the use of intratympanic corticosteroids in MD.^7^ In this review, 10 randomised controlled trials (RCTs) and quasi-RCTs comparing intratympanic corticosteroids, all using dexamethasone, compared with either placebo or no treatment were included. The authors found that the evidence for the use of dexamethasone is uncertain. Intratympanic dexamethasone injection may marginally reduce the frequency of vertigo attacks. Regarding hearing and tinnitus, improvement was seen but without statistical significance.

The most commonly intratympanically administered corticosteroids are dexamethasone and methylprednisolone.^1^ Phillips *et al*^8^ determined the efficacy of intratympanic OTO-104 (a sustained-released dexamethasone hydrogel) for the treatment of MD, in three double-blind, placebo-controlled RCTs, with a total of 165, 174 and 148 patients respectively. OTO-104 showed numerically larger decreases in definitive vertigo days compared with placebo across all three studies. However, in only one study, this difference was statistically significant. Pharmacokinetic studies show that dexamethasone phosphate has molecular and pharmacokinetic characteristics that complicate its use as a topical therapy for hearing disorders, which may explain its questionable effectiveness.^9^ An animal study found that the concentrations of methylprednisolone are higher and have longer duration in perilymph and endolymph compared with dexamethasone and hydrocortisone, and therefore, could be a more effective drug.^10^ Typically, soluble forms of methylprednisolone are administered and expected to be less permeable through the membranous boundaries compared with the less polar forms. However, there is no data whether these soluble forms are metabolised to the base form in the ear and if they are, at what rate.^9^ Despite the fact that little is known about the pharmacokinetics of methylprednisolone, there are clinical indications of its effectiveness.^11 12^ Cao *et al*^12^ performed a literature review and demonstrated that methylprednisolone is more effective than dexamethasone in a clinical setting.

Although in the last decade, there is an increasing tendency and emerging evidence for the use of intratympanic steroids, no large RCT on the effectiveness of intratympanic methylprednisolone in MD has been conducted.^13^ A meta-analysis published in 2021 included eight studies comparing intratympanic gentamicin to intratympanic corticosteroids, in which gentamicin appeared to be superior in terms of control of vertigo attacks.^14^ However, gentamicin is known to be ototoxic and can induce hearing loss. Patel *et al*^15^ compared intratympanic gentamicin injections to methylprednisolone injections in a double-blind RCT with a 24-month post-treatment follow-up. Vertigo attacks decreased in both groups, indicating a treatment effect. However, no placebo group was involved and the sample size was relatively small (n=60).

In conclusion, there is a need of solid evidence on the effectiveness of intratympanic steroids in MD. Until now, the effectiveness of methylprednisolone has not been investigated by means of a placebo controlled RCT. Therefore, a well-conducted RCT with a large study population and a long follow-up period is now required to evaluate the effectiveness of intratympanic methylprednisolone in MD. In this protocol, we present the methods of a phase-3 multicentre, double-blinded, randomised, placebo-controlled trial evaluating the effectiveness of intratympanic injections with methylprednisolone vs placebo in the treatment for MD patients.

## Methods

### Trial design

In this phase 3, multicentre, double-blind, placebo-controlled randomised trial, the effect of two intratympanic methylprednisolone sodium succinate 62.5 mg/mL (Solu-Medrol in Act-O-Vial, Pfizer BV) injections 14 days apart is compared with two placebo (ie, sodium-chloride 0.9%) injections with the same time interval on vertigo attacks in patients with MD. Parallel groups will be randomly assigned to one of both arms and outcomes will be measured during a 1 year follow-up period.

To ensure transparency and completeness in this clinical trial, the SPIRIT and CONSORT checklists are provided in onlinesupplemental files 1  2.

### Study subjects

Patients with MD will be recruited by six participating sites in the Netherlands and will be approached by their own ENT specialist and informed about this trial. After a 1 week reflection period, informed consent forms can be signed. Baseline and outcome data will be extracted from participants’ electronic medical records and collected in the cloud-based clinical data management platform Castor EDC (version v2023.1.0.1, LUMC).

### In- and exclusion criteria

In order to be eligible for the study, a study subject needs to have unilateral, definite MD according to the diagnostic criteria derived from the American Academy Otolaryngology Head and Neck Surgery, Classification Committee of the Bárány Society, European Academy of Otology and Neurotology and International Classification of Vestibular Disorders published in 2015.^16^ The criteria for definite MD are:

Two or more spontaneous episodes of vertigo, each lasting 20 min to 12 hours,

AND

Audiometrically documented low-frequency to medium-frequency sensorineural hearing loss in one ear, defining the affected ear on at least one occasion before, during or after one of the episodes of vertigo,

AND

Fluctuating aural symptoms (hearing, tinnitus or fullness) in the affected ear (not better accounted for by another vestibular diagnosis).

Other inclusion criteria are:

Age >18 years at the start of the trial.≥ 4 vertigo attacks over the last 6 months.Willing to adhere to daily completion of study questionnaires using the DizzyQuest app and to the follow-up assessments.

Study subjects who meet any of the following criteria will be excluded:

Bilateral MD.Severe disability (eg, neurological, orthopaedic, cardiovascular) or serious concurrent illness that might interfere with treatment or follow-up.Active additional neuro-otologic disorders that may mimic MD (eg, vestibular migraine, recurrent vestibulopathy, phobic postural vertigo, vertebro-basilar TIAs, acoustic neuroma).Otitis media with effusion based on tympanogram results.History of intratympanic injections with corticosteroid less than 6 months ago.History of intratympanic injections with gentamicin or ear surgery for treating MD.Pregnant women or nursing women.

### Sample size

A sample size calculation was performed based on recommendations as summarised in the Clinical Practice Guideline for Menière’s disease.^1^ An expected proportion of subjects achieving vertigo control of 87.5% was assumed for methylprednisolone treatment compared with an assumed 67.5% for placebo, that is, a difference in treatment effect of 20%. With a statistical power (1-β) of 80% and a type 1 error (α) of 5%, 67 patients per group are required. With an estimated 10% loss-to-follow-up, 74 patients will be included in each arm, giving a total sample size of 148. In total, over the six participating centres, 340 MD patients yearly visit the Otolaryngology department and will be screened for the trial. It is expected that 15% will meet the inclusion criteria and will be willing to participate. This will result in approximately 50 eligible patients for inclusion per year.

### Randomisation and blinding

Subjects will be randomly assigned to either methylprednisolone or placebo with a 1:1 allocation as per computer-generated random sequence, stratified by site generated by Castor EDC. Blinding will be maintained until all subjects have finished their treatment phases. All study participants, participating medical professionals and outcome assessors will be blinded. The independent epidemiologist and pharmacy personnel will both be unblinded during randomisation and therapy allocation.

### Study procedure

After a 1 week reflection period and agreement with trial participation by means of signing the informed consent, a patient will be seen at the study site. Standard inquiries about the patient’s demographics, family history and medical history—particularly regarding any history of autoimmune disease and migraine—are made at the informed consent visit. Thereafter, patients will receive an intratympanic injection with either methylprednisolone or placebo at day 1 and day 15 with a window of 3 days. The patient is lying down in supine position with their head rotated to the side and prior to the intratympanic injection, the eardrum will be anaesthetised. Thereafter, a myringotomy is being performed and a small spinal puncture needle is passed through the tympanic membrane to inject fluid into the middle ear cavity at the level of the round window. The patient is then required to remain on their side without swallowing for 30 min.

At baseline, results of MRI must be available to make sure other causes of disease are ruled out.^17^ To assess the vestibular function of the horizontal semicircular canals, the caloric test and video head impulse test (vHIT) will be performed. To evaluate the anterior and posterior semicircular canals, the vHIT will be conducted at baseline in order to assess the presence of vestibular hypofunction or areflexia.

During a follow-up period of 1 year, overall well-being and vertigo attacks are being assessed daily with the aid of the DizzyQuest app. Two telephone contacts will take place at 3 and 6 months to assess possible (serious) adverse events, DizzyQuest app compliance and the use of escape medication or co-interventions. A physical follow-up visit in the outpatient clinic will be scheduled at 6 and 12 months. During these outpatient clinic visits, additional audiometry and multiple questionnaires concerning tinnitus, dizziness and quality of life will be filled-in. An overview of follow-up moments of the corresponding outcomes and a flowchart of the study procedure are presented in table 1 and figure 1, respectively.

**Figure 1 F1:**
[figure not shown]
Flowchart of the study procedure. IT, intratympanic.

**Table 1 T1:** Overview of follow-up moments of the corresponding outcomes

Moment in trial	Type of follow-up	Outcomes
From moment of inclusion unit 1 year follow-up		Daily questionnaire in DizzyQuest app
Baseline	First intratympanic injection	Baseline parametersMRIOtoscopyAudiometry PTA and SDS Vestibular testing vHIT, caloric testing Questionnaires DHI, TFI, FLS, EQ-5D/VAS, iMCQ, iPCQ
2 weeks	Second intratympanic injection	OtoscopyComplicationsUse of co-interventionsUse of escape medication(S)AE
3 months, 9 months	Telephone consult	ComplicationsUse of co-interventionsUse of escape medication(S)AE
6 months, 12 months	Consult in outpatient clinic	OtoscopyComplicationsAudiometry PTA and SDS Questionnaires DHI, TFI, FLS, EQ-5D/VAS, iMCQ, iPCQ Use of co-interventions Use of escape medication (S)AE

DHI, Dizziness Handicap Index; EQ 5DEuroQol 5DFLS, Functional Level Scale; HIT, head impulse test; iMCQ, iMTA Medical Consumption Questionnaire; iPCQ, iMTA Productivity Cost; PTA, pure tone average; (S)AE, (Serious) Adverse EventSDS, Speech Discrimination ScoreTFITinnitus Functional Index

### Outcome measures

#### Vertigo

The primary outcome measure will be defined by the class of vertigo as defined by the AAO HNS 1995 guideline. The class of vertigo is defined by the average number of attacks per month during 6 and 12 months after treatment divided by the number of attacks 6 months before treatment times 100. As a result, the following class of vertigo is defined:

A: Complete control of vertigo=0.B: Substantial control of vertigo=1–40.C: Limited control of vertigo=41–80.D: Insignificant control of vertigo=81–120’.E: Worse control of vertigo >120.

Moreover, the daily attack vertigo frequency will be monitored with the aid of the DizzyQuest app (Psymate 2).^18 19^ The DizzyQuest app will be used to track the primary outcome measure, the frequency of dizziness attacks. Patients will answer daily questionnaires about their health and well-being and patients can report vertigo attacks at any time using the DizzyQuest app. Additionally, the Dizziness Handicap Inventory (DHI) questionnaire will be administered at baseline, after 6 months and after a year to assess how dizziness affects daily life.^20^ The effect of the injections in the DHI will be reported as raw data, as well as change in handicap category (mild handicap, moderate handicap or severe handicap) related to improvement, unchanged or worsened.

The following secondary outcomes will be measured.

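### As printed, the vertigo score divides a monthly average by a six-month count, so an unchanged patient scores 16.7 and falls in class B

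*Protocol article*

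**What the plan says.** In the protocol article, Outcome measures, Vertigo, the primary outcome is the AAO-HNS 1995 class, and the article then writes out its own formula. The score is given as "average number of attacks per month during 6 and 12 months after treatment divided by the number of attacks 6 months before treatment", multiplied by 100.

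The score is then cut into bands. A score of 0 is class A. The others are "B: Substantial control of vertigo=1–40", "C: Limited control of vertigo=41–80", "D: Insignificant control of vertigo=81–120" and "E: Worse control of vertigo >120".

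The Statistical analysis section names this class as the primary outcome, to be analysed by ordinal mixed-model regression. It adds an analysis of the recorded attack counts by generalised estimating equations (GEE), giving an incidence rate ratio. Table 2 lists both the count and the class under primary outcome. The inclusion criteria express the baseline attack count as a six-month total (at least 4). No section puts the pre-treatment term on a monthly basis.

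**The concern.** The numerator carries both the averaging and the monthly unit; the denominator carries neither. Read as written, the score is a rate per month over a total per six months. The bands belong to a different scale. The band labelled insignificant surrounds 100 and the band labelled worse starts above 120, so 100 has to mean no change. The formula and its labels cannot both be right.

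The sentence defines a primary outcome. A programmer who followed it would put unchanged patients, and patients up to 2.4 times worse, in the second-best class. The ordinal analysis would lose most of the information in the lower classes.

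**Working it through.** **The plan's own figure.** The article works no example of the vertigo score. Its only related calculation is the sample size: 87.5% versus 67.5%, 80% power, α = 5%, giving 67 per group.

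- Pooled variance, two-sided: [1.96·√(2·0.775·0.225) + 0.8416·√(0.875·0.125 + 0.675·0.325)]² / 0.20² = 67.2, or 68 rounded up.
- Unpooled variance: 7.849·0.32875/0.04 = 64.5, or 65 rounded up.
- Power with 67 per group is 79.9%. Adding 10% gives 67·1.10 = 73.7, hence 74 per arm.

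The stated 67 is reproduced to within rounding. It starts from assumed control proportions and does not use the score formula.

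**Score as written.** Let b be the attacks in the six months before treatment and f the ratio of the post-treatment to the pre-treatment attack rate. The post-treatment monthly average is f·b/6.

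- As written: 100·(f·b/6)/b = 100·f/6 = 16.7·f. The baseline b cancels, so the factor is the same for every patient.
- With both terms per month: 100·(f·b/6)/(b/6) = 100·f.

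| Change in attack rate | As written | Class | Both per month | Class |
|---|---|---|---|---|
| None left (f = 0) | 0 | A | 0 | A |
| Halved (f = 0.5) | 8.3 | B | 50 | C |
| Unchanged (f = 1) | 16.7 | B | 100 | D |
| Doubled (f = 2) | 33.3 | B | 200 | E |
| Tripled (f = 3) | 50 | C | 300 | E |

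Example: with 6 attacks in the six months before and 12 in the six months after, the score as written is 2/6·100 = 33.3 (B). On a common base it is 2/1·100 = 200 (E).

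**Where the classes end as written.** Set 100·f/6 equal to each upper limit:

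- B ends at f = 40·6/100 = 2.4.
- C ends at f = 80·6/100 = 4.8.
- D ends at f = 120·6/100 = 7.2, so class E needs more than a 7.2-fold increase.

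**What literal scoring would do to power.** This part needs inputs that the article does not give. Only the entry minimum of 4 attacks, the 67.5% and 87.5%, and n = 67 per arm come from it. Assumed: Poisson counts; median baseline of 8 or 12 attacks per six months; between-patient baseline SD of 0.6 on the log scale; patient-level response SD of 0.8 or 1.2 on the log scale; and arms calibrated so that 67.5% and 87.5% are in class A or B when both terms are per month.

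| Quantity, over the four scenarios | Both per month | As written |
|---|---|---|
| A or B, placebo | 67.5% | 97.0–99.4% |
| A or B, methylprednisolone | 87.5% | 99.6–99.9% |
| Power, rank test on five classes, one assessment | about 88–92% | about 53–76% |
| Power, two-proportion test of A or B versus the rest | about 80% | about 8–21% |

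The rank test is a simple stand-in for the ordinal mixed model. As written, classes C to E together hold at most 3% of placebo patients (100 − 97.0). A score of zero is zero in either unit, so membership of class A does not change. The remaining power comes almost entirely from the contrast between A and B.

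**The case against.** The strongest reply is that the intended scale can be recovered. The article says that the class follows the cited guideline, the bands are centred on 100, and the Statistical analysis section speaks of percentage decreases. The monthly average in the first half of the sentence can be read as carrying over to the second. On that reading the sentence is a loose paraphrase and nobody would score the data the wrong way. This stands as far as intent goes: a monthly rate in both terms is the probable meaning. It does not make the printed formula right. The article goes beyond the citation and writes out a rule. Condensing a protocol explains missing detail, but not a stated formula that contradicts its own bands.

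A second reply is that the other analysis listed as primary, the GEE of attack counts, never uses this score. That is correct, and it limits the damage.

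A reader might also infer that the error would destroy the trial's power, with the 80% behind the sample size falling to 8–21%. The document does not support that. Those figures belong to a two-proportion test that takes vertigo control to mean class A or B. Neither the Sample size section nor the interim rule under Patient safety defines control in that way, and the planned analysis of the class is ordinal. If control meant class A alone, the unit error would not alter it.

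**Conclusion.** The definition is wrong as written. That an unchanged patient scores 16.7 and lands in class B is exact, needs no assumption beyond reading the sentence as printed, and holds for every baseline count. It contradicts the article's own bands.

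The finding concerns the text. It does not show that data have been or will be mis-scored. If the formula were applied literally, classes C to E would be nearly empty and the ordinal comparison would lose power, from about 88–92% to about 53–76%. That range rests on assumed baseline and patient variability, on calibrating the two control proportions to classes A and B, and on a rank test at a single assessment. The class A contrast, the GEE of counts and the sample-size figure are unaffected.

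**What to change.** State the denominator as the average number of attacks per month during the six months before treatment, so that both terms have the same unit and 100 means unchanged. Adding that an unchanged patient scores 100 and falls in class D would let any programmer check the code against the text. If the full protocol or SAP repeats the sentence, make the same change there.

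The cost is one phrase. No data item, visit or patient is affected, and the sample size stays as it is.
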